### Quantitative analysis

Patients participating in the PGAP trial are heterogeneous in terms of specific back pain problems, length of time in pain, history of attending pain management programmes and current medical management, including medication. Therefore, participating patients’ age, gender, marital status, length of time in pain, medical diagnosis (if any), number of pain sites, previous medical or therapeutic procedures and current medication is be gathered as potentially useful explanatory variables in all analyses.

The longitudinal change in the response variables of interest across treatment arms will be analysed using a linear mixed model to compare the change within individual participants (that is, before and after the intervention) and between the study arms (that is, comparing the cohort of patients who received the PGAP intervention to the control group participants), adjusting for baseline, treatment centre and patient characteristics as necessary. It will be assumed that missing data are missing at random, and the sensitivity to this assumption will be assessed using multiple imputations based on chained equations [35].

The selection of explanatory variables for inclusion in all final models will be based on a combination of clustering, tree-based methods and variable selection techniques applied to the complete cases and to the imputed data. All analyses will be carried out using R software [36] and SPSS software (SPSS Inc, Chicago, IL, USA) as necessary.

Model-checking will be performed using suitable model diagnostics and residual plots. Sensitivity analysis will be used to explore whether adherence to the intervention influences the effect of the intervention on the primary outcome.

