**Methods and design:**

Adult patients (ages 18 years and older) with nonmalignant back pain who are work-disabled because of chronic pain and not involved in litigation in relation to their pain were invited to take part. Patients were those who show at least one elevated psychosocial risk factor (above the 50^th^ percentile) on pain disability, fear-based activity avoidance, fatigue, depression or pain catastrophizing. Following screening, patients are randomised equally to the intervention or control condition within each of the seven trial locations. Patients allocated to the control condition receive usual medical care only. Patients allocated to the PGAP intervention condition attend a maximum of 10 weekly individual sessions of structured active rehabilitation in addition to usual care. Sessions are delivered by a clinical psychologist and focus on graded activity, goal-setting, pacing activity and cognitive-behavioural therapy techniques to address possible barriers to rehabilitation.

The primary analysis will be based on the amount of change on the Roland Morris Disability Questionnaire posttreatment. We will also measure changes in work status, pain intensity, catastrophizing, depression, fear avoidance and fatigue. Outcome measures are collected at baseline, posttreatment and 12-month follow-up. Health-related resource use is also collected pre- and posttreatment and at 12-month follow-up to evaluate cost-effectiveness.

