### Sample size

Following published guidelines [22], the sample size calculation was based on having 80% power at the 5% significance level to detect a difference in mean post-treatment improvement of 3 units or more on the Roland-Morris Back Pain Questionnaire between the control and intervention groups, assuming that the standard deviation of the improvement is 6.1 units in both groups [14]. In order to ensure sufficient power to detect such a difference, a sample size of 60 is needed for each arm. However, allowing for an attrition rate of 15% [16], and based on the experience of [name] *et al*. (personal communication [name], September 2007), we aim to include 140 participants (70 per group) in the study and expect to have complete data for about 120 participants following dropouts.

Screening of larger numbers of patients will be required to obtain a sample of 140. On the basis of recent research examining the prevalence of psychosocial risk factors among a general practice population, where at least one factor was found in 24% of respondents and up to 52% had a particular risk indicator, we expect that 20% to 50% of our sample frame will have one or more of the psychosocial risk factors [23].

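### The primary mixed model gives baseline two roles and leaves adjustment for baseline and centre conditional, so it permits a model in which baseline adjustment does nothing for the treatment estimate

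*Protocol article*

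**What the plan says.** All references are to the protocol article; no separate analysis plan is shown.

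- **Quantitative analysis.** "The longitudinal change in the response variables of interest across treatment arms will be analysed using a linear mixed model", whose purpose is "to compare the change within individual participants (that is, before and after the intervention") and also between study arms, "adjusting for baseline, treatment centre and patient characteristics as necessary". The same section then chooses explanatory variables for every final model by clustering, tree-based methods and variable selection. It does not exempt baseline or centre.
- **Abstract, Methods and design.** "The primary analysis will be based on the amount of change on the Roland Morris Disability Questionnaire posttreatment". "Outcome measures are collected at baseline, posttreatment and 12-month follow-up".
- **Sample size.** "80% power at the 5% significance level" for "a difference in mean post-treatment improvement of 3 units or more", "assuming that the standard deviation of the improvement is 6.1 units in both groups", leading to 60 per arm with complete data.
- **Randomisation and treatment allocation.** Blocks are generated separately by site, so centre is the stratification factor.

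**The concern.** A before/after comparison within participants suggests that the baseline score is one of the responses. Adjusting for baseline suggests that it is a covariate. Each is sound alone, but the sentence asks for both in one model and does not say which is meant.

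Done together, they conflict. A covariate that is constant over time within a person shifts all of that person's fitted values equally, so it cannot adjust a treatment-by-time contrast. The analysis would look baseline-adjusted while giving the unadjusted change-score estimate and forgoing the precision that adjustment should bring. In some fits the standard error is wrong as well.

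The qualifier at the end of the sentence, followed by data-driven selection, adds a second looseness: whether baseline and the stratification factor are in the primary model may depend on the data.

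**Working it through.** **Inputs from the protocol article:** difference 3 units, SD of improvement 6.1, 60 per arm, 5% significance, 80% power. **Assumed:** two-sided test (sidedness is not stated); correlation ρ between baseline and follow-up of 0.3, 0.5 and 0.7 (not in the document); equal variance at each visit; complete data.

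**1. The plan's own figure.** n per arm = 2(1.96 + 0.842)² × 6.1² / 3² ≈ 65 (66 by t-test; 52 if one-sided). The stated 60 is not reproduced. That is a separate sample size matter and says nothing about how baseline is used. It does explain why change-score power at 60 per arm is below 80%.

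**2. Change-score precision and power at 60 per arm.** SE = 6.1 × √(2/60) = 1.114. Power ≈ Φ(3/1.114 − 1.96) = 76.8% (t-test 76.2%).

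**3. ANCOVA at 60 per arm.** If the change has SD 6.1, the residual SD of follow-up given baseline is 6.1 × √((1+ρ)/2). The change-score variance is therefore 2/(1+ρ) times the ANCOVA variance. Powers are by noncentral t.

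| ρ | Residual SD | SE | Variance ratio | Power |
|---|---|---|---|---|
| 0.3 | 4.92 | 0.90 | 1.54 | 91% |
| 0.5 | 5.28 | 0.96 | 1.33 | 87% |
| 0.7 | 5.62 | 1.03 | 1.18 | 83% |

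**4. Baseline as response row and covariate, two visits, random intercept, with group, time and group-by-time.** Let s² be the variance at each visit.

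- The common baseline slope averages 1 (baseline rows) and ρ (follow-up rows), giving (1+ρ)/2.
- The covariance of a person's two residuals is then −s²(1−ρ)²/4. It is negative, so the random-intercept variance is estimated at 0.
- The pooled residual variance is s²(1−ρ)(3+ρ)/4, so the model variance of the interaction is s²(1−ρ)(3+ρ)/n.
- The true variance of the change-score difference is 4s²(1−ρ)/n.
- Hence model SE / true SE = √((3+ρ)/4), and type I error = 2[1 − Φ(1.96 × ratio)].

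| ρ | SE ratio | Type I error, formula | Type I error, simulated |
|---|---|---|---|
| 0.3 | 0.91 | 7.5% | 7.4% |
| 0.5 | 0.94 | 6.7% | 6.5% |
| 0.7 | 0.96 | 5.9% | 5.8% |

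The simulations used 3,000 trials per setting, with 60 per arm and no treatment effect. The estimate equalled the raw change-score difference in every run (maximum difference 0), and the intercept variance was 0 in every run.

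**5. The same model with the 12-month visit added** (equal correlation between visits). The estimate is still the raw change-score difference. The SE is right: ratio 0.99 to 1.01, simulated type I error 4.8% to 5.2%.

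**6. Baseline used once.** ANCOVA: simulated type I error 4.8% to 5.5%. Baseline as response only: SE 1.11, type I error about 5%.

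**The case against.** The strongest reply is that the text never says that baseline rows stay in the response vector. The before/after words may only explain what change means. The Abstract, the Hypothesis section and the Sample size section all treat change or improvement as the outcome, and change adjusted for baseline gives the same treatment estimate as ANCOVA of the post-treatment score. On that reading there is no lost precision and no faulty standard error. This stands: the ANCOVA-type reading is open.

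A reader might infer something stronger, that the planned standard errors are too small and the primary test rejects too often. The document does not support that. The inflation in step 4 needs double use of baseline, a two-visit data set, a random-intercept structure and a group main effect, and none of these is stated. Outcomes are also collected at 12 months, and with that visit in the same model the inflation is absent. Nor is the 76% to 77% power evidence of double use, since it follows from 60 per arm being too few for the stated inputs.

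It can also be said that the response vector and covariance structure belong in an analysis plan, and that the qualifier may attach only to patient characteristics. The first is fair for detail that is merely left out. But here the article itself states two roles for baseline that should not be combined in this form of model. On the second, the grammar allows either scope, and the selection step that follows covers all final models without exempting baseline or centre.

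**Conclusion.** The point holds as an ambiguity with a real cost on one of its readings. The wording permits a primary model in which baseline adjustment has no effect on the treatment estimate, and it can be read as making baseline and the stratification factor optional.

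Under double use with group, time and their interaction, the loss is the gap between change-score and ANCOVA power at 60 per arm: about 76% to 77% against 91%, 87% and 83% at ρ of 0.3, 0.5 and 0.7. If the model is also restricted to two visits with a random intercept, the standard error is 4% to 9% too small and type I error is about 7.5%, 6.7% and 5.9%. These figures rest on the assumed correlations, a two-sided test and complete data. They describe what the wording allows and do not establish what will be fitted. No general claim of inflated type I error follows.

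**What to change.** State that baseline RMDQ is used once in the primary model, in one of two ways:

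- **Covariate:** responses are the post-baseline RMDQ scores (post-treatment and 12 months), with baseline RMDQ, treatment, time and treatment-by-time as fixed terms. The post-treatment contrast is primary.
- **Response:** baseline RMDQ stays in the response vector with the arm means constrained equal at baseline, and there is no baseline covariate.

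In either case always include randomisation centre. Remove the conditional qualifier for baseline and centre, and say that both are exempt from the variable selection step.

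The cost is wording only. Baseline RMDQ is already collected and centre is already the stratification factor, so no further patients or data are needed.

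### The sensitivity analysis named for the missing-at-random assumption itself assumes missing at random, as described, so it does not show what happens if that assumption fails

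*Protocol article*

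**What the plan says.** The Quantitative analysis section says that the response variables "will be analysed using a linear mixed model to compare the change within individual participants" and between arms, with adjustment for baseline, centre and patient characteristics as needed. On missing data it states: "It will be assumed that missing data are missing at random". The same sentence goes on to say that "the sensitivity to this assumption will be assessed using multiple imputations based on chained equations".

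The section mentions two related things, and neither is a departure from MAR. The imputed data are also used for covariate choice ("variable selection techniques applied to the complete cases and to the imputed data"). The only other sensitivity analysis concerns adherence: "Sensitivity analysis will be used to explore whether adherence to the intervention influences the effect of the intervention on the primary outcome".

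The Sample size section gives the expected loss, "allowing for an attrition rate of 15" per cent, with 70 recruited per group and about 120 participants expected to have complete data.

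**The concern.** A likelihood-based mixed model gives valid estimates when missingness is MAR given the data in the model. Chained-equations imputation, unless modified, draws each missing value from conditional models fitted to the observed data, so it needs the same kind of assumption. Setting one beside the other changes the computation, and perhaps the set of variables conditioned on. It does not change the assumption that, given those variables, unseen outcomes behave like seen ones.

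What is at stake is how the robustness statement can be read. Outcomes are self-reported on postal questionnaires, so non-response could depend on the unseen outcome. If the two analyses agreed, the report could say that sensitivity to MAR had been examined when no scenario in which MAR fails had been looked at.

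**Working it through.** **1. The two analyses side by side.**
- Main analysis: linear mixed model, stated to assume MAR.
- Check: multiple imputation by chained equations, with no delta shift, pattern-mixture model, selection model or reference-based imputation mentioned anywhere in the article.
- Stated object of the check: the MAR assumption.

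Both analyses rest on MAR, so the object of the check is not varied.

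**2. Inputs from the Sample size section.** Standard deviation of improvement 6.1 in both groups; target "a difference in mean post-treatment improvement of 3 units or more"; 60 evaluable per arm; 15% attrition; "80% power at the 5% significance level" (taken as two-sided, which is not stated). The article gives no figure for the missing-data check itself. Its attrition step reproduces: 60/(1 − 0.15) = 70.6, in line with 70 per group, and 140 × 0.85 = 119, in line with about 120. The 60 per arm is used here as stated. Whether it follows from the other inputs is a separate question.

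**3. What a departure from MAR would do (illustration).** Let missing patients in an arm improve by d points less than MAR predicts, and let p be the fraction missing. Then

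overstatement of the effect = p(PGAP) × d(PGAP) − p(control) × d(control).

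- Shift in the PGAP arm only, p = 0.15: 0.15 per point of d. For d = 3, 0.15 × 3 = 0.45 points, or 15% of the 3-point target. For d = 6, 0.15 × 6 = 0.90 points, or 30%.
- Equal shifts with equal missingness, for example d = 3 in both arms: 0.45 − 0.45 = 0.
- Shift in the control arm only: the sign reverses and the effect is understated.

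**4. Tipping point for the PGAP-only case.** Unadjusted SE = 6.1 × √(2/60) = 1.114. Significance limit = 1.96 × 1.114 = 2.18. For an observed effect of 3.0 and the SE held fixed: (3.0 − 2.18)/0.15 = about 5.4 points. That is 5.4/6.1 = about 0.9 SD and 5.4/3 = 1.8 times the target.

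**5. Simulation under assumed conditions.** 70 per arm, SD 6.1, baseline-outcome correlation 0.5, true effect −3 (negative favours PGAP), about 15% missing in each arm, 1,000 replicates and 20 imputations. Missingness depended on the unseen outcome in the PGAP arm and was random in the control arm.

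| Analysis | Mean estimate |
|---|---|
| Complete data, before deletion | −3.04 |
| Observed-data likelihood (baseline-adjusted) | −3.86 |
| MAR imputation, same predictors | −3.85 |
| Imputation, PGAP shift 3 | −3.40 |
| Imputation, PGAP shift 6 | −2.94 |

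The two MAR estimates differ by 0.07 on average in absolute value (correlation 0.996), and both miss the complete-data value by about 0.8. Only the shifted imputations move, by (3.85 − 3.40)/3 = 0.15 per point, which matches step 3. The imputation used the same predictors as the likelihood analysis, so the close agreement is built in. The simulation shows that agreement is possible when MAR is false, not that this trial's two analyses would agree.

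**The case against.** The strongest reply is that chained equations are an engine and not an assumption. Shifted imputations run on the same engine, the stated purpose is compatible with them, and a condensed article may leave the shifts to an analysis plan that is not shown. The paper cited for the method is not at hand either. This stands as far as it goes: if shifts are specified elsewhere, one sentence settles the point. But the article names both a method and a purpose, and the method as described does not serve the purpose. That is more than an omitted detail.

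A second reply is that MAR is conditional. Imputation could draw on the other questionnaire scales, the mid-treatment measures in the intervention arm, and medication and service use, so it could differ from the mixed model and show whether the narrower conditioning set is adequate. This is correct and is a good reason to keep the imputation. It still leaves MAR in place, given the wider set.

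A reader might infer that the check is bound to agree with the main result and so give false reassurance. The documents do not support that, because auxiliary variables could move the estimate.

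A reader might also infer that PGAP patients who fare badly are the likely dropouts, so that the effect is overstated. The documents do not support that either. The Progressive Goal Attainment Program section allows sessions to end early when a patient can return to work, so some who stop early have improved. Outcomes are collected by post in both arms, so leaving sessions is not the same as missing the outcome. No attrition by arm or by reason is given.

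**Conclusion.** The point holds in this form: the article promises an assessment of sensitivity to MAR and names for it an analysis that, as described, also assumes MAR. What happens if MAR fails is therefore not assessed. No analysis of the observed data can test MAR, and the article does not claim to. The shortfall is that no departure from MAR is examined.

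The conclusion rests on reading the imputation as unmodified, since no modification is stated. The 0.15 points per point of shift and the tipping point of about 5.4 illustrate scale only. They assume 15% missing, a shift in the PGAP arm alone, a fixed unadjusted SE and an observed effect of exactly 3.0. On that example the result would withstand a fairly large departure, and with similar shifts in both arms the bias would largely cancel. The documents establish neither the direction of missingness nor its dependence on arm. The primary model is not in question.

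**What to change.** Describe chained-equations imputation as an alternative MAR analysis and list the auxiliary variables it will use. Name as the sensitivity analysis at least one prespecified missing-not-at-random analysis. A suitable choice is delta-adjusted imputation of the Roland-Morris outcome, with the shift varied separately in each arm over a stated range (0 to 6 points would cover the illustration above) and the tipping point reported. Control-based imputation for PGAP patients with missing outcomes is an optional addition. If such shifts are already specified in an analysis plan, a sentence saying so is enough.

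The cost is a little extra analysis work: a few lines of code on imputations already planned, and no new data.

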### Medication and health service use

Medication and health service use will be measured at baseline, posttreatment and follow-up for all patients. They will be measured using the pain version of the Client Service Receipt Inventory (CSRI) [31]. This will provide information on medication and health service resource use. The CSRI has been used widely in economic cost-of-illness studies, including studies of chronic pain [5,32,33], and has been validated as an accurate measure of frequency of health service use [34]. Medication use is likely to vary throughout the trial duration, and GPs will be allowed to vary medication as they see fit. However, change in medication use will be measured in post-treatment analysis. In cases of potential dual-use medication being taken by a patient, we will, with the patient’s consent, confirm with the prescribing GP if the medication was prescribed for pain or otherwise. Additional information will be gathered on (1) demographic variables (age, education, marital status); (2) pain-related information (duration of pain, number of pain sites, recurrence of pain, previous attendance at a pain management programme); and (3) details of any comorbid health conditions.

A patient is deemed suitable to go forward to the treatment allocation stage of the trial based on the presence of elevated psychosocial risk factors. This is defined as a score above the 50th percentile on any of the five risk factors targeted by the intervention: catastrophizing (Pain Catastrophizing Scale), fear of movement (Fear-Avoidance Beliefs Questionnaire), disability (Roland-Morris Disability Questionnaire), depression (Hospital Anxiety and Depression Scale) and fatigue (Fear and Fatigue Scale).

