### Randomisation and treatment allocation

Eligible participants (that is, those who show elevated psychosocial risk factors) will be randomly assigned by computer-generated block randomisation to ‘intervention’ (PGAP sessions plus MTAU) or ‘control’ (MTAU only). We expect 20 participants to take part in the trial in each of the seven trial centres. Therefore, block randomisation with variable block sizes is used to minimize the occurrence of chance imbalance in allocation to treatment and control and to preserve unpredictability. The sequence of the different blocks is predetermined by an independent researcher not involved in the trial and concealed to all investigators. The blocks are generated separately for the different study sites so that stratification according to trial centre can be performed. It was decided to stratify on trial centre only for pragmatic reasons. Stratifying on additional variables, although useful, would have called for a larger sample. As each treating psychologist was seeing these trial patients in addition to their usual caseload, a limit was placed on the number of patients each clinician would be asked to see, thus limiting stratification.

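### The covariates of the primary Roland-Morris model are left to data-driven selection with no fixed set, so the 5% error rate is not guaranteed

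*Protocol article*

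**What the plan says.** The abstract fixes the primary comparison: "The primary analysis will be based on the amount of change on the Roland Morris Disability Questionnaire posttreatment". The Sample size section plans it with "80% power at the 5% significance level" and about 120 completers.

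The Quantitative analysis section describes a linear mixed model, "adjusting for baseline, treatment centre and patient characteristics as necessary". A later paragraph of that section says how covariates enter: "The selection of explanatory variables for inclusion in all final models will be based on a combination of clustering, tree-based methods", together with "variable selection techniques applied to the complete cases and to the imputed data". The scope is all final models, with no exception for the primary one.

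The candidates are in the same section, in a list ending "current medication is be gathered as potentially useful explanatory variables in all analyses". It names eight: age, gender, marital status, pain duration, diagnosis, number of pain sites, previous procedures and current medication. The Medication and health service use section adds education, comorbid conditions and "pain-related information (duration of pain, number of pain sites, recurrence of pain, previous attendance at a pain management programme"), of which recurrence and previous programme attendance are new.

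Centre is the only stratification factor: "The blocks are generated separately for the different study sites so that stratification according to trial centre can be performed".

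**The concern.** The trial has one main confirmatory test, and the covariates in its model are to be found by a search of the trial data. Three families of methods are applied to two versions of the data, and these can select different sets. The article does not say which set then becomes the primary model, or whether the search is made without sight of allocation.

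This is a stated rule, not a detail left to an analysis plan. A later plan that fixed the primary covariates would have to depart from it.

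Two things are at stake. If treatment is in the model during the search, the selected covariates can depend on chance imbalance between the arms, and the final test then rejects slightly too often. If several selected models are available and one is chosen after the treatment effects have been seen, the false-positive rate rises further.

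A smaller point concerns current medication. It is a candidate with no time point given, while medication is measured at baseline, posttreatment and follow-up and may be changed by the GP during the trial. A baseline value is the natural reading, but the rule does not exclude a value measured after randomisation.

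**Working it through.** **Inputs from the protocol**
- Nominal level 5% (two-sided assumed; sidedness is not stated); 1:1 allocation.
- Completers: 140 × (1 − 0.15) = 119, stated as about 120.
- Candidates: 8 in Quantitative analysis. Adding education, recurrence, previous programme and comorbidity gives 8 + 4 = 12. Counts of 20 and 30 are stress tests; they could arise only if diagnosis, procedures or medication were split into many terms.

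**Assumed, not in the protocol**
- Candidates explain either none or 20% of the outcome variance, and baseline explains 25%.
- Covariates are independent and normal. There is one post-treatment outcome, no missing data and no centre effect.
- Forward selection and p-value screening stand in for the selection step. Trees and clustering were not simulated.

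**Model under no treatment effect**

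y = 0.5·B + Σ βⱼCⱼ + e, with β₁ = β₂ = β₃ = √(R²/3), the other β = 0, and Var(e) = 0.75 − R².

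Treatment and baseline B are always in the final model. The result is the share of runs in which the treatment coefficient has p < 0.05.

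**Simulation error around 5%:** ±1.96·√(0.05 × 0.95 / N), which is ±1.1 points for N = 1,500, ±0.7 for 4,000 and ±0.5 for 8,000.

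**Results**

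| How the covariates are fixed | Candidates | Type I error |
|---|---|---|
| Prespecified set (the plan's 5%, reproduced) | 8 to 30 | 4.1–5.5% |
| Automatic selection, blind to arm | 8 to 30 | 4.6–5.7% |
| Automatic selection, treatment in the selection model | 8 | 5.1–6.0% |
| Same | 12 | 5.6–6.6% |
| Same | 20 | 6.3–7.0% |
| Same | 30 | 7.0–7.8% |
| Most favourable of three selected models (forward selection, screening at p < 0.05, screening at p < 0.20) | 8 to 12 | 5.8–7.1% |
| Most favourable of all sets of up to 3 covariates | 8 | 9.1–13.5% |

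The three-model row comes from a check at 4,000 runs per setting. The last row used 1,500 runs per setting and searches 1 + 8 + 28 + 56 = 93 models.

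**Reading.** The first two rows cannot be told apart from 5% within simulation error. With the candidates that the protocol lists, an automatic search with treatment in the model adds at most about 6.5 − 5 = 1.5 percentage points. Only free choice among models reaches 13.5 / 5 = 2.7 times the nominal level.

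**The case against.** The strongest reply is that the written rule need do no harm. A combination of methods can mean one consolidated selection, run without sight of allocation, and that version holds the 5% level in the simulations. The approach was announced before the analysis, while follow-up was still being collected, so the plan is not post hoc; only the resulting model would depend on the data. The algorithm, thresholds and blinding may stand in an analysis plan that is not shown. All of this is fair, and it limits the size of the point. It does not remove it, because the published rule applies to every final model and keeps no fixed model as primary.

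A reader might also infer four stronger things that the document does not support:
- **That covariates are chosen on the outcome.** The text says only that the techniques are applied to the complete cases and the imputed data. Tree and selection methods normally use the response; clustering need not.
- **That standard errors will ignore the selection.** No method for standard errors is described, so this is a guess.
- **That error rates near or above 10% follow from the plan.** They follow from picking the most favourable model, which the text does not say will be done.
- **That centre may be dropped and that this would inflate false positives.** Centre is named as an adjustment, and the words on necessity may qualify patient characteristics only. In a simulation with seven centres and an assumed centre share of 5% to 20% of the variance, omitting centre lowered the type I error to between 4.5% and 3.5%. That is conservative.

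**Conclusion.** The point holds in a limited form. The covariate set of the primary model is not fixed, and the stated rule does not say how it will be settled, so control of the 5% level cannot be verified from the plan. It would be wrong to say that the level is known to be broken. Inflation is nil or nearly so if selection is automatic and arm-blind. It is modest, about 5% to 6.5%, if treatment is in the selection model with 8 to 12 candidates. It is about 6% to 13% only if analysts can choose among the resulting models. These figures rest on assumed covariate strength and on a simplified single-visit model with stepwise selection and screening. Severity: should-fix.

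**What to change.** Before outcomes are examined by arm, state one primary model:
- Roland-Morris score at the post-baseline assessments on treatment, time and treatment-by-time, with the posttreatment contrast as the primary test.
- Baseline Roland-Morris score and randomisation centre always included.
- A short list of baseline covariates, named by the investigators on prior grounds, none measured after randomisation. The document gives no basis for preferring particular variables, so the choice is theirs.

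Use the same set for the complete-case and imputed analyses, so that the two differ only in how missing data are handled. Move clustering, tree and variable-selection models to secondary, sensitivity or exploratory analyses, reported apart from the primary test.

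The cost is a change of wording, with no new patients or data and no change to the sample size. The small downside is losing any precision that a data-chosen covariate might have added.
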